**Fig. 4 Fig4:**
[figure not shown]
The schedule of enrolment, interventions, and assessments

#### Outcome measures

The CTS-6 is a validated questionnaire inquiring about severity, frequency, and duration of symptoms—including nocturnal and daytime pain and numbness or tingling—experienced by the patient in the past two weeks [17]. Each item has five possible response options, which range from 1 (no symptom) to 5 (most severe symptom). The symptom score is the mean of all answered items; higher scores (1 to 5) indicate worse symptoms. The *Quick*DASH is a short form of the disabilities of the arm, shoulder, and hand (DASH) questionnaire, a widely used outcome measure for upper extremity disorders, including CTS [18]. The *Quick*DASH consists of 11 items concerning difficulties in performing activities with five response options (from no difficulty to unable to perform an activity). Higher score (0 to 100) indicates worse activity limitations. The EuroQol 5-dimensions (EQ-5D) is a widely used measure of general health and quality of life; the EQ-5D-5 L version will be used [19]. The palmar pain scale is a two-item scale measuring pain in the palm and related activity limitations; higher score (0 to 100) indicates more pain and activity limitations [20]. Treatment satisfaction will be measured with a visual analog scale asking the patients to rate (on a scale of 0 to 100) their satisfaction with their current hand status with regard to symptoms and ability to use it in daily activities (higher score indicates higher satisfaction).

#### Physical examination

The physical examinations will be performed by an orthopedic specialist and will include measurement of 2-point discrimination (performed on the radial and ulnar aspects of each digit) and measuring grip strength with the Jamar dynamometer and pinch strength with the pinch gauge (three trials for each hand). The examiner will be blinded to group allocation, and at the 12-month follow-up, the palm will be covered to conceal possible surgical scars.

#### Nerve conduction tests

Median nerve conduction testing of the study hand will be carried out by a trained research nurse and interpreted by a neurophysiologist, both blinded to the clinical status. The measurements include median nerve distal motor latency and wrist-digit distal sensory latency in the index finger (median nerve), ring finger (median and ulnar nerves), and small finger (ulnar nerve). The results are classified as normal or as mild, moderate, or severe median neuropathy (Table 1) in accordance with standard neurophysiological criteria [21, 22].

**Table 1 Tab1:** Classification of nerve conduction testing results

Grade	Motor latency^a^	Sensory latency^b^	
		Peak latency difference (index-small)^c^	Inter-peak latency (ring)
Normal	Normal	<0.6	Single peak
Mild	Normal	≥0.6	≥0.6
Moderate	Abnormal	>1.2	>1.0
Severe	Abnormal	Absent response	Absent response

All values are in milliseconds. A result is classified as abnormal if one or more criteria are present

^a^Distal motor latency values according to age-based reference limits. (For example, values of more than 4.2 ms for age of 30 years and of more than 4.3 ms for age of 50 years are considered abnormal.)

^b^Median-ulnar sensory latency difference

^c^Index finger peak latency values above 3.8 ms (women) and 4.0 ms (men) are considered abnormal

#### Adherence

In written information before randomization and during all contacts with the research team, the trial participants will be informed about the importance of adhering to the allocated intervention.

#### Measurement of actual splint and bandage use

Both the rigid splint and the soft bandage will be fitted with a temperature-monitoring device that registers temperature variations according to whether the splint or bandage is in contact with the skin (Fig. 2). The Thermochron^®^ iButton^®^ device (Maxim Integrated, San Jose, CA, USA) is a small disk recording the temperature at predefined intervals and stores the results in a protected memory section. This type of temperature sensor is commonly used to monitor the cold chain of the food industry and also for pharmaceutical and medical products; a similar device has been previously used in clinical research [23, 24]. The device records temperature ranging from −40 °C to 85 °C with measurement accuracy of 1 °C. In this study, the recording intervals will be set at 40 min. After 6 weeks of splint use, the disc will be removed and the measurements will be uploaded to a computer. At the conclusion of the trial, the duration and pattern of wearing the splint will be computed and analyzed.

#### Surgery

The decision to choose to have surgery will be made by the patient, on the basis of the experienced severity of current symptoms and activity limitations, in consultation with an orthopedic surgeon not involved in the trial and blinded to the patient’s group allocation. Surgery will be performed by specialists in orthopedics or hand surgery not involved in the trial, in accordance with usual practice at the department.

### Assessments of efficacy

#### Primary endpoints (in rank order)

Change in the 6-item CTS symptoms score from baseline to 12 weeksRate of surgery at 52 weeks

#### Secondary endpoints

Change in the 6-item CTS symptoms score from baseline to 6 weeks and 52 weeksChange in *Quick*DASH score from baseline to 12 weeks and 52 weeksChange in patient satisfaction score at 12 weeks and 52 weeksChange in EQ-5D index from baseline to 12 weeks and 52 weeksCost-effectiveness at 52 weeksPalmar pain score at 52 weeksTime to surgery within 52 weeksDuration of sick leave during 52 weeksChange in grip strength from baseline to 52 weeksAdverse events at 52 weeks

### Assessment of safety

During the conduct of the trial, the investigator will report all adverse events. All adverse events will be followed up until resolved or as clinically required. Adverse events may be reported spontaneously by the patient or elicited through open questioning during and at the end of the trial. Participants will be informed to contact the trial therapists or coordinator whenever they wish to discuss or report any events during the intervention. In addition, they will be able to report adverse events at the 6-week follow-up and any subsequent follow-up. All reported or observed adverse events, including type, intensity, and duration, will be recorded in a standard protocol. Any serious adverse events will be promptly reported to the steering and data monitoring committees and the trial sponsor.

### Assessment of costs

The costs of the rigid splint and soft bandage and the visits to therapist will be calculated. Cost for sick leave will be estimated by multiplying the number of days by the estimated mean income for the profession of that patient. In case of unemployment, a fixed rate will be used and for patients on maternity leave, cost will be calculated as for the working patients.

### Staff information and documentation

All personnel involved with the trial will be informed orally and in writing about the trial procedures. Case report forms (CRFs) will be provided for recording of all data. Accuracy of the data on each CRF will be attested by the examiner’s signature. If any assessments are omitted, the reasons will be noted on the CRFs. The patients’ responses to questionnaires will be checked for completeness by the examiner or trial coordinator. All data will be stored in the department’s databases accessed only by the trial researchers.

### Withdrawals

Patients will be able to withdraw from the trial at any time without need to give reasons. Patients who do not wish to attend physical examination will be asked to complete the questionnaire.

### Sample size

In a previous study, patients with idiopathic CTS improved on average by 1.6 points in the CTS-6 score (range of 1 to 5) at 12 weeks after surgery [20]. No previous data regarding change in CTS-6 score after use of wrist splinting or soft bandage are available. A score improvement of 0.7 corresponds to improvement by one severity level in four of the six items (i.e., from severe to moderate, moderate to mild, or mild to no symptoms, in more than half of the items). If the soft bandage is assumed to have no effect, it would correspond to “no treatment”. A previous study found that the mean change in CTS-6 score in a group of patients who completed the CTS-6 on two occasions with 1–3 weeks’ interval *without treatment* was 0.03 (95% confidence interval (CI) of −0.07 to 0.12) [17]. With 90% power, 5% significance level, two-sided tests, and mean changes (baseline to 12 weeks) in the CTS-6 score of 0.7 in the splint group (standard deviation of 0.9) and 0.1 in the soft-bandage group, a sample of 48 patients per group will be needed. To account for possible dropouts, we plan to recruit 112 patients.

### Statistical analysis

For continuous endpoints (CTS-6, *Quick*DASH, patients satisfaction, palmar pain, EQ-5D index, grip strength, time to surgery, and sick leave duration), mean values and standard deviations will be calculated. For categorical variables (rate of surgery and adverse events), proportions will be calculated. Statistical tests will be performed in accordance with the intention-to-treat principle. An exploratory as-treated analysis will also be performed.

Both hypothesis-generating and confirmatory testing will be performed, the latter for the primary endpoints. Multiplicity issues will be addressed in compliance with the European Medicines Agency’s Guideline on multiplicity issues in clinical trials. More specifically, the primary endpoints are ranked according to clinical relevance, and confirmatory claims will not be based on an endpoint with a rank lower than the variable whose null hypothesis was the first that could not be rejected. The subgroup analyses will be carried out in rank order.

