### Interventions

#### Group A: Splint with metal bar

The patients will receive a standard splint (model Base, Catell AB, Hägersten, Sweden) with wrist in neutral position to be worn at night and, if possible, during the day (Fig. 2). No other instructions or treatments will be given. If after 6 weeks the patient reports large improvement, no further treatment will be given. If the patient reports small or no improvement, further treatment with the same splint will be given for 4 weeks. If the patient reports small or no improvement after 10-week splinting, the patient will be offered surgery. Patients who refuse further treatment with wrist splinting will be offered surgery. Surgery will not be performed before 12 weeks after treatment start.

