#### Primary analyses

The change in CTS-6 score from baseline to 12 weeks (primary outcome) will be compared in the two groups by using mixed model analysis of repeated measures and adjusting for the baseline score. The rate of surgery at 52 weeks (co-primary outcome) will be compared by using Cox regression analysis with fixed follow-up time and the Huber–White estimator [25, 26] and adjusting for age, dominance of the study hand, and baseline CTS-6 score; relative risks with 95% CIs will be calculated. As supportive analysis the chi-squared test will also be performed.

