#### Secondary analyses

Mean changes in *Quick*DASH score, EQ-5D index, and grip strength over time (from baseline to 52 weeks) will be compared by using mixed model analysis of repeated measures and adjusting for respective baseline values. Mean treatment satisfaction and palmar pain scores at 12 and 52 weeks will be compared between the groups by using the *t* test. Mean total duration of sick leave from treatment start to 52 weeks will be calculated and compared by using Satterthwaite’s *t* test. Time to surgery (in days) will be analyzed by constructing Kaplan–Meier curves and comparing the groups with the log-rank test. Cost-effectiveness will be analyzed by using the incremental cost-effectiveness ratio. Three subgroup analyses will be carried out (in rank order): baseline CTS-6 score (≥3.0 versus <3.0), baseline nerve conduction results (severe/moderate versus mild/normal), and symptom duration (≥6 versus <6 months). Adverse events will be presented in tables. A *P* value of 0.05 will indicate statistical significance.

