### Missing values

For the patient-reported measures, missing item responses will be managed in accordance with the instructions specific to each scale. If the number of missing items precludes calculating a score, the missing score will not be replaced. Missing values for other variables will not be replaced.

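### Time to surgery is listed for a mean and standard deviation although patients not operated on by week 52 have no observed time: a minor error in the descriptive summary of a secondary endpoint

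*Protocol article*

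**What the plan says.** In the protocol article, the opening paragraph of Statistical analysis lists the continuous endpoints and their summary. Time to surgery is on that list: "time to surgery, and sick leave duration), mean values and standard deviations will be calculated".

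Secondary analyses then handles the same endpoint as censored event-time data: "Time to surgery (in days) will be analyzed by constructing Kaplan–Meier curves and comparing the groups with the log-rank test".

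Other sections bear on how the two statements fit together:

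- Secondary endpoints limits the endpoint to surgery within 52 weeks.
- Surgery is elective: "The decision to choose to have surgery will be made by the patient". Some patients can be expected to have none.
- Both intervention sections set a floor: "Surgery will not be performed before 12 weeks after treatment start".
- Withdrawals: "Patients will be able to withdraw from the trial at any time without need to give reasons".
- Missing values, for variables that are not patient-reported: "Missing values for other variables will not be replaced".
- Primary analyses covers the surgery rate at 52 weeks separately. It "will be compared by using Cox regression analysis with fixed follow-up time and the Huber–White estimator", with relative risks and 95% CIs, and a chi-squared test in support.

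**The concern.** A mean and SD need a value for every patient, or a stated rule for those without one. A patient who reaches week 52 unoperated has only a lower bound. The article gives no rule, and two readings are open.

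- **Operated patients only.** An unoperated patient's time is blank, and the no-replacement rule could lead an analyst to leave it so. The arms are then compared on subsets selected by what happened after randomization. The result describes timing given surgery and says nothing about how many had surgery.
- **Unoperated patients entered at last follow-up.** With complete follow-up this is the restricted mean to 52 weeks, a sound quantity if labelled as such. A patient who withdraws early is instead counted as if operated on at withdrawal, which shortens the apparent time.

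At stake is the number printed for this endpoint. The log-rank test yields a P value and no effect size, and the relative risk concerns the rate of surgery. The mean and SD is therefore the only numerical summary of time to surgery that the article names.

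**Working it through.** **The plan's own figures.** The article gives no surgery rate, event count or sample size for time to surgery. Its sample size concerns the CTS-6 change: 2 × (1.960 + 1.282)² × 0.9² / 0.6² = 47.3, so 48 per group. That reproduces, and this point does not touch it. Below I use only the planned 112 patients (56 per group) against the 96 needed, a dropout allowance of 16, or 8 per group.

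**Inputs.** From the article: earliest surgery at 12 weeks (day 84) and a window of 52 weeks (day 364), which leaves 280 days. Assumed: the proportion p operated on by day 364 and the distribution of surgery times.

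**A. Identical uniform timing in both arms, complete follow-up.** The operated-only mean is (84 + 364)/2 = 224 days in each arm, whatever p is. The restricted mean is p × 224 + (1 − p) × 364.

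| Assumed p, splint / bandage | Operated-only mean (days) | Restricted mean (days) | Gap in restricted mean |
|---|---|---|---|
| 25% / 40% | 224 / 224 | 329 / 308 | 21 |
| 30% / 60% | 224 / 224 | 322 / 280 | 42 |

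The zero gap in operated-only means follows from assuming the same timing in both arms. It is a limiting case.

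**B. Constant hazard from day 84, complete follow-up.** The hazard is λ = −ln(1 − p)/280, and the operated-only mean is 84 + 1/λ − 280(1 − p)/p.

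- p = 30%: 84 + 785.0 − 653.3 = 215.7 days. Restricted mean: 0.3 × 215.7 + 0.7 × 364 = 319.5.
- p = 60%: 84 + 305.6 − 186.7 = 202.9 days. Restricted mean: 0.6 × 202.9 + 0.4 × 364 = 267.3.

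The operated-only gap is 12.8 days (SDs about 81 and 79) and the restricted-mean gap is 52.2 days. Over the whole assumed range of p from 20% to 80%, the operated-only mean moves only from 219 to 188 days, while the restricted mean moves from 335 to 223.

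In 5,000 simulated trials of 56 per group at 30% versus 60%, the log-rank test was significant at 5% in 91% of runs. A t test on operated-only times was significant in 8%, and a t test with unoperated patients set to day 364 in 85%. No t test of time to surgery is planned; these shares only show how much of the contrast each summary carries.

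**C. Last follow-up as the value, with withdrawals.** Take the 30% / 60% row of A. Assume 8 of 56 patients withdraw at day 84, with the same prognosis as the rest of their arm, and are entered as 84. The arm mean falls by (8/56) × (restricted mean − 84).

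- Splint: 322 − (1/7) × 238 = 288.
- Bandage: 280 − (1/7) × 196 = 252.

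With withdrawals in both arms the gap shrinks from 42 to 36 days. With withdrawals in the splint arm only, it is 288 − 280 = 8 days. In the 25% / 40% row the splint mean becomes 329 − (1/7) × 245 = 294 against 308, so the direction reverses. Withdrawal at day 84 is the earliest time that matters under the floor if nobody leaves sooner; later withdrawal distorts less.

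**The case against.** The strongest reply is that nothing inferential depends on this sentence. It is a general list of descriptive statistics. The specific plan for the endpoint is Kaplan–Meier with a log-rank test, which handles censoring. That stands. A reader might infer that the trial's conclusion on surgery is at risk; the documents do not support this, because neither the log-rank test nor the analysis of the surgery rate uses the mean.

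A reader might also infer that the reported mean must be wrong or must hide a difference. That goes too far. With unoperated patients counted at week 52 and complete follow-up, the mean is the restricted mean and shows the difference, as the table in A demonstrates. Nor would a difference be hidden from readers of the full report, since the proportions operated on, the relative risk and the curves would show it.

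An operated-only mean also need not contradict the Kaplan–Meier curve, because it answers a different question. The splint arm's extra four weeks before the surgery offer might suggest a built-in shift in that mean. Yet the first scheduled offers in both arms (after 6 and 10 weeks) precede the shared 12-week floor, and the documents give no basis for sizing any such effect.

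Finally, an analysis plan that is not shown may define the handling. This has less force: the article does not leave the summary open but names one, and the one named does not suit the endpoint.

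**Conclusion.** The point holds as a minor error. The article summarises a censored endpoint by a mean and SD in one section and treats it as censored in another, with no rule that reconciles the two. An operated-only mean can hide much of a group difference (about 13 days shown against 52 under constant hazard at 30% versus 60%) or all of it (0 against 42 days under identical timing). A mean with last follow-up entered as the value is valid only when follow-up to 52 weeks is complete; eight early withdrawals in one arm could cut the gap from 42 to 8 days or, at 25% versus 40%, reverse it.

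The surgery rates, timing distributions and withdrawal pattern are all assumptions, used because the documents supply none. The defect itself does not depend on them. The consequence is confined to the description of one secondary endpoint.

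**What to change.** Delete time to surgery from the list of endpoints described by mean and SD in Statistical analysis. In Secondary analyses, add that it will be summarised from the Kaplan–Meier curves by the surgery-free proportion in each group at 52 weeks and, as the effect size, the difference in restricted mean surgery-free time to 52 weeks with a 95% CI, with patients who withdraw unoperated censored at their last follow-up. If a mean among operated patients is shown, label it as such and do not use it to compare the groups.

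The cost is a change of wording. The dates of surgery and last follow-up are already required for the planned curves. Sample size, tests and trial conduct do not change.

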#### Primary analyses

The change in CTS-6 score from baseline to 12 weeks (primary outcome) will be compared in the two groups by using mixed model analysis of repeated measures and adjusting for the baseline score. The rate of surgery at 52 weeks (co-primary outcome) will be compared by using Cox regression analysis with fixed follow-up time and the Huber–White estimator [25, 26] and adjusting for age, dominance of the study hand, and baseline CTS-6 score; relative risks with 95% CIs will be calculated. As supportive analysis the chi-squared test will also be performed.

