### Randomization

Patients will be randomly assigned in accordance with a computer-generated randomization list (ratio of 1:1) [16]. The randomization will be stratified in accordance with patient sex and carried out in random blocks of various sizes (4, 6, and 8). An administrative assistant, not involved in the trial, will prepare sequentially numbered sealed opaque envelopes containing the group allocation. After providing written informed consent and undergoing the baseline assessment by a study investigator (orthopedic surgeon), the enrolled patient will proceed to the hand therapist, who will open the envelope with the lowest number and provide the patient with either a wrist splint with a metal bar or a soft bandage in accordance with treatment allocation (Fig. 1).

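### Sex stratifies the randomization but is left out of both primary models; adjusting for it would recover a small amount of precision if sex is prognostic

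*Protocol article*

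**What the plan says.** Protocol article, Randomization: allocation follows a "computer-generated randomization list (ratio of 1:1"), and "The randomization will be stratified in accordance with patient sex and carried out in random blocks of various sizes (4, 6, and 8"). No other stratification factor is named.

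Protocol article, Primary analyses:
- The 12-week CTS-6 change is compared "by using mixed model analysis of repeated measures and adjusting for the baseline score".
- Surgery at 52 weeks is compared with "Cox regression analysis with fixed follow-up time and the Huber–White estimator", "adjusting for age, dominance of the study hand, and baseline CTS-6 score".
- "As supportive analysis the chi-squared test will also be performed", with no mention of stratification.

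Protocol article, Secondary analyses: time to surgery is handled by "constructing Kaplan–Meier curves and comparing the groups with the log-rank test", again unstratified. The mixed models for QuickDASH, EQ-5D index and grip strength adjust for their own baseline values only.

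Sex appears in no analysis, no sex-adjusted sensitivity analysis is described, and no reason is given. Because the adjusters are listed by name, this is a stated choice and not a detail left to a later analysis plan.

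**The concern.** Blocking within sex makes the two arms more alike on sex than simple randomization would. Any part of the outcome that sex explains therefore contributes almost nothing to the true sampling variation of the treatment difference. A model without sex still counts that part as residual noise, so its standard error exceeds the true one. The usual rule is to analyse by the factor that restricted the randomization. Here the surgery model includes age and hand dominance, which did not restrict it, and omits sex, which did.

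What is at stake is efficiency: intervals somewhat too wide, a real significance level somewhat below 5%, and some lost power. It touches both primary endpoints because they are tested in rank order, so a conservative CTS-6 test also reduces the chance of reaching a confirmatory claim on surgery.

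**Working it through.** **Inputs from the protocol article (Sample size).** Mean CTS-6 changes 0.7 and 0.1 (difference 0.6); SD 0.9, stated for the splint group and taken as common to both; two-sided 5%; 90% power; 48 per group.

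**Assumed inputs.** The article gives neither the sex mix of the trial nor a sex effect on outcome.
- Share of women p = 0.70. The Background gives prevalences of about 5% in women and 2% in men; with equal numbers of each sex that is 5/7 = 71%.
- Sex difference d in CTS-6 change, beyond the covariates already in the model: 0 to 0.7.

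**Step 1: the plan's own figure.** n = 2 × 0.9² × (1.960 + 1.282)² / 0.6² = 47.3, so 48 per group. SE = 0.9 × √(2/48) = 0.1837, and power = Φ(0.6/0.1837 − 1.960) = 90.4%. The stated 48 is reproduced and takes no credit for sex adjustment.

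**Step 2: effect of leaving sex out of the CTS-6 model.** Hold the total within-arm SD at 0.9. Sex explains R² = p(1 − p)d²/0.9². With k = √(1 − R²):
- true SE under stratified allocation ≈ 0.1837k, while the model without sex reports about 0.1837
- true alpha without sex = 2[1 − Φ(1.960/k)]
- power without sex = Φ[(Δ/0.1837 − 1.960)/k]
- power with sex = Φ[Δ/(0.1837k) − 1.960]

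Example, d = 0.5: R² = 0.21 × 0.25/0.81 = 0.065, k = 0.967, and alpha = 2[1 − Φ(2.027)] = 4.3%.

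| d | R² | Reported SE too large by | True alpha without sex | Power at 0.6, without / with sex | Power at 0.4, without / with sex |
|---|---|---|---|---|---|
| 0 | 0 | 0% | 5.0% | 90.4% / 90.4% | 58.6% / 58.6% |
| 0.3 | 0.023 | 1.2% | 4.7% | 90.7% / 91.1% | 58.7% / 59.6% |
| 0.5 | 0.065 | 3.4% | 4.3% | 91.2% / 92.2% | 58.9% / 61.5% |
| 0.7 | 0.127 | 7.0% | 3.6% | 91.9% / 93.8% | 59.2% / 64.5% |

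The loss is about 0 / 0.4 / 1 / 2 points at the planned 0.6. If the true difference is only 0.4, it is about 1 / 3 / 5 points for the three non-zero effects.

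**Step 3: simulation check.** Sex-stratified blocks of 4, 6 and 8, N = 96, 70% women. For d = 0.3 / 0.5 / 0.7, type I error was 4.7 / 4.2 / 3.6% without sex and 4.9 / 4.8 / 5.0% with it. Power at 0.6 (20,000 runs per scenario) was 90.3 / 90.7 / 91.1% without and 90.7 / 91.7 / 93.1% with. Power at 0.4 was 56.5 / 58.0 / 57.9% without and 57.6 / 60.8 / 63.1% with.

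**Step 4: sensitivity to the sex mix.** With 50% to 80% women and d = 0.45 (half an SD), the reported SE is 2% to 3% too large.

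**Step 5: surgery.** Modified Poisson regression with a robust SE stood in for the fixed-time Cox model; N = 112, 4,000 runs per scenario, none of the other planned covariates. The surgery risks by sex (women / men) are assumptions.

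| Assumed risk | Alpha without / with sex | Power at RR 0.6 without / with sex |
|---|---|---|
| 60% / 60% | 4.7% / 4.7% | 72.1% / 72.1% |
| 65% / 50% | 4.4% / 4.8% | 72.0% / 72.2% |
| 70% / 40% | 3.4% / 4.5% | 73.6% / 75.0% |

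In the last row the mean robust SE under the null was 0.152 against an empirical 0.147, so the Huber–White estimator does not remove the mismatch. The Monte Carlo error on these alphas is about √(0.05 × 0.95/4000) = 0.3 points.

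**The case against.** The strongest reply is that this costs the trial almost nothing. Every consequence depends on sex predicting outcome, and the article gives no such effect: its only figures by sex are population prevalences. Only what sex explains beyond the baseline score counts, and the calculations above do not model the baseline covariate separately. A sex difference of 0.7 would exceed the whole planned treatment effect of 0.6. At 0.1 to 0.2 the power difference is 0.2 points or less. The sample size already delivers 90% without sex adjustment, so what is forgone is a bonus. The secondary tests carry no confirmatory claim, so stratifying them adds little. All of this stands, and it limits the finding to a small one.

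It does not remove the point. The omission is explicit, the direction is certain whenever sex is prognostic, and nothing is saved by leaving sex out. The Discussion reports mostly small symptom changes with splinting, so a true difference below 0.6 is not far-fetched, and that is where the lost power is larger.

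A reader might infer something stronger: that the primary tests are invalid, that the standard errors are certainly wrong, or that the trial is underpowered. The documents support none of these. The error can only be conservative, the treatment estimate is not biased by it, and at the planned difference the calculated power stays at or above 90%.

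**Conclusion.** The point holds as a small, conditional loss of efficiency. Sex is the only stratification factor, and it is absent from both primary models and from the chi-squared and log-rank tests.

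For CTS-6 at the planned difference, the cost runs from nothing (sex not prognostic) to about 2 points of power and a true alpha of about 3.6% (sex difference 0.7). It can reach about 5 points if the true difference is 0.4. For surgery it was at most 1.4 points, under an extreme assumed contrast in risk by sex.

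These sizes rest on assumptions that the article cannot confirm: about 70% women, a common SD of 0.9, and the stated sex effects taken as net of the other covariates. The surgery figures are the least secure, since they use a stand-in model without the planned covariates.

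**What to change.** Before the data are analysed, prespecify sex as a fixed covariate in the CTS-6 mixed model and in the surgery relative-risk model (or stratify that model by sex). For consistency, add sex to the secondary mixed models, use the Mantel-Haenszel form of the supportive chi-squared test stratified by sex, and stratify the log-rank test by sex.

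The cost is a line of wording and one degree of freedom per model. No new data are needed, because sex must be known for every patient before allocation. Adding it only after the results are seen would look data-driven.
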